# Clinical efficacy of iodine complex in SARS-CoV-2-infected patients with mild to moderate symptoms: study protocol for a randomized controlled trial

**DOI:** 10.1186/s13063-021-05848-8

**Published:** 2022-01-19

**Keywords:** Iodine, COVID-19, SARS-CoV-2

## Abstract

**Background:**

Coronavirus disease 2019 (COVID-19) caused by the novel coronavirus-infected millions globally. Despite a wide range of advised options for the treatment of COVID-19, a single strategy to tackle this pandemic remains elusive, thus far. That is why we are conducting a clinical trial to find out the efficacy of iodine complex to clear a viral load of severe respiratory syndrome coronavirus-2 (SARS-CoV-2) along with a reduction in time taken to alleviate symptoms.

**Discussion:**

The study is designed to measure the superior efficacy of the iodine complex as an add-on in treating COVID-19-positive patients with mild to moderate symptoms. This combination is hypothesized to improve various parameters like rapid viral load reduction, clinical and radiological improvement, lower mortality, and reduction in hospitalization. The trial will aid in devising a better strategy to cope with COVID-19 in a relatively inexpensive and accessible way. The implications are global, and this could prove itself to be the most manageable intervention against COVID-19 especially for patients from limited-resource countries with deprived socioeconomic status.

**Trial registration:**

ClinicalTrials.govNCT04473261. Registered on July 16, 2020.

## Administrative information

**Table Taba:** 

Title {1}	Clinical efficacy of iodine complex in SARS-CoV-2 infected patients: study protocol for a randomized controlled trial
Trial registration {2a and 2b}.	Clinical Trial registration is at www.clinicaltrials.gov with ID **NCT04473261** dated July 16, 2020.
Protocol version {3}	Protocol Version Number is 2.4 dated 10/02/2021
Funding {4}	Shaikh Zayed Post-Graduate Medical Complex and Smile Welfare Organization

## Introduction

### Background and rationale {6a}

As the world was still recovering from The Great War, mayhem which shook the world and killed more than 40 million soldiers and civilians, mother earth suffered from a pandemic of influenza. This deadly virus, in a year, spread everywhere on earth and diseased roughly 500 million and killed 100 million people. Surprisingly after the 101st anniversary of that horrendous plague, we are again witnessing a fast-spreading, highly infectious severe respiratory syndrome coronavirus-2 (SARS-CoV-2) sweeping across the continents. This disease first originated in Wuhan, China, in December 2019 which was later called coronavirus disease 2019 (COVID-19). The illness was declared a pandemic by the World Health Organization (WHO) in March 2020 [1, 2]. Despite being huge data available on the virus epidemiology, pathophysiology, virology, diagnosis, prevention, and management, still most of the available management options are unable to provide promising results and this demands a dire need to find a cure for this highly contagious virus.

Despite this wide range of options available for the treatment of COVID-19, none has been proven to be a definitive therapy against this virus. This makes it the need of the hour to think outside the box and prescribe newer formulations and conduct trials for treating COVID-19. This makes it the need of the hour that a novel idea of using micronutrients should also be proposed as an antiviral in this trial.

Micronutrients are also essential for the body to produce enzymes, hormones, and other substances essential for proper growth and development [3]. Their deficiencies have been reported in many diseased states. Diet deficient in these nutrients may lead to compromised humoral and cell-mediated immunity [4]. Iodine is considered an excellent antimicrobial and specifically antiviral action of the elements commonly used in nutrition [5–7]. Cell culture studies also show that higher concentrations of iodine have exceptional antiviral activities. The potential of iodine against human immunodeficiency virus (HIV) has been tested due to its powerful antiviral activity [8]. It highlighted some important aspects of the mechanism of action of iodine as an antiviral agent [9]. Moreover, through scientific studies, it has been established that iodine complexes circulate throughout the body in the extracellular fluids found between the cells of the body. If cell surface proteins have the amino acid tyrosine on the outside, the passing iodine complex reacts with this tyrosine. This reaction denatures the proteins and thus kills the abnormal cell. Intra-membrane proteins may have tyrosine which is only exposed when the membrane is distorted by abnormal cell development. So, the iodine complex supports the surveillance system for removing abnormal cells from our bodies. Iodine complex inactivates viruses by interfering with the protein coat of the virus hence the ability of the viruses to adsorb to host cell is impaired. Iodine complex also triggers a mechanism for apoptosis (normal programmed death of cells as part of their life cycle) a process for destroying cells that present a threat to the integrity of the organism, like cells infected with viruses [9].

Potassium iodide boosts not only the humoral immune system of the body by increasing immunoglobulin production but also increases peripheral lymphocytes level which is important in the host response against viruses. Supplementation of potassium iodide is essential for enhancing humoral immunity against pathogens [10].

In vitro studies were conducted on the antiviral properties of iodine complex against severe respiratory syndrome coronavirus-2 (SARS-CoV-2) at the University of Veterinary and Animal Sciences, Lahore, Pakistan, which showed strong to moderate antiviral activity [11]. Another in vitro trial has suggested the antiviral activity of povidone-iodine against SARS-CoV-2 when exposed for more than 60 s and can be used in various concentrations in oral and nasal formulations [12]. Consistent with that is an in vitro study published in *JAMA* showed that the use of povidone-iodine at different concentrations successfully deactivated the COVID-19 virus in only 15 s as compared to 70% ethanol used as control which failed to do so [13]. This was also observed in the past in SARS-CoV and Middle Eastern Respiratory Syndrome (MERS) in which iodine-containing preparations showed the same virucidal effect as 70% ethanol as control [14].

With the unsettling trend of coronavirus worldwide, it is considered to evaluate iodine complex as a potentially affordable and accessible remedy to mitigate infection [15].

### Objectives {7}

The objective of the study is to measure the efficacy of the ionic-iodine polymer complex in reducing the length of the symptomatic phase along with earlier SARS CoV-2 clearance and radiologically better chest as compared to the placebo group in mild to moderately symptomatic patients.

### Trial design {8}

This is a placebo-controlled, multi-armed, add-on to standard therapy, interventional, randomized trial using a parallel group design. It is closed-labeled, adaptive with sample size reassessment, and multi-centered with a 1:1:1:1 allocation ratio design with a superiority framework.

## Methods: participants, interventions, and outcomes

### Study setting {9}

Clinical sampling will be done from Shaikh Zayed Post-Graduate Medical Complex, Ali Clinic and Doctors Lounge, Lahore, Pakistan.

### Eligibility criteria {10}

All COVID-19 diagnosed and declared non-pregnant adults with mild to moderate illness will be recruited in the study. Patients with acute or chronic ailments, who are breastfeeding, or with history of iodine allergy will be excluded from the trial. Patients not giving consent will also be eliminated.

### Who will take informed consent? {26a}

The site investigator will take written informed consent from all trial participants by giving them the specifically constructed informed consent form. The consent will be taken on the recruitment site after explaining the procedure to the participants in detail.

### Additional consent provisions for collection and use of participant data and biological specimens {26b}

Site investigators will be responsible for taking consent regarding every other matter if required. An informed consent form will contain a section on permission to draw and conduct specified tests on blood samples and conduct radiological investigations as per the protocol of the study.

## Interventions

### Explanation for the choice of comparators {6b}

All patients will be assigned in 4 arms at the time of randomization. Placebo comparator group, arm X, will receive a placebo empty capsule, in addition to standard care. Interventional arms A, B, and C will be given ionic-iodine polymer complex (200 mg of elemental iodine) in 3 different formulations (capsule, syrup, and nasal spray, respectively). These formulations are being tested for comparative effectiveness and evaluation of the best possible route of administration.

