### Intervention description {11a}

In this multi-armed study, ionic-iodine polymer complex will be given using three formulations with 200 mg of elemental iodine to evaluate efficacy for a maximum of 14 days or when the patient is fully recovered.
Arm A will be receiving 200 mg iodine complex capsule three times a dayArm B will be receiving iodine complex suspension syrup form 40 ml three times a dayArm C will be receiving iodine complex nasal spray 2 puffs three times a day.Arm X will be receiving a placebo of empty capsule three times a day.

All patients will receive standard care as per version 3.0 of clinical management guidelines for COVID-19 established by the Ministry of National Health Services of Pakistan COVID-19 guidelines of the study setting.

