### Strategies to improve adherence to interventions {11c}

To improve adherence to the intervention, participants will be counselled about the advantages of this study. All the participants will be monitored regarding compliance to their assigned treatment strategy and health professionals will administer the drugs. As this trial will include quarantined patients, hence direct observational method will be sufficient to make sure compliance and adherence to the interventions.

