## Assignment of interventions: blinding

### Who will be blinded {17a}

Trial participants, care providers, outcome assessors, and data analysts are blinded, respectively, by using placebo group, by using site investigators to provide placebo or drugs to participants, by using blinded clinicians to assess the clinical outcome and laboratory or radiological findings, and by using analysts from other institution that are not having any conflict of interest in research. The details will be announced after locking the data in a database sheet at the end of the trial.

The study experimental drug and placebo will be prepared by the team of pharmacists and pharmacologists in the Department of Pharmacology and Toxicology, University of Veterinary and Animal Sciences, Lahore, Pakistan. Both drugs will look alike, as they will have same packing but unique randomization codes. Participants, site investigators, care providers, outcome assessors, study coordinators, data managers, and statisticians will be blinded, and blinding codes will be revealed at the end of this study.

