### Procedure for unblinding if needed {17b}

Unblinding is permissible if the patient develops severe symptoms and needed extra treatment by revealing a participant’s allocated intervention during the trial. If unblinding is required, the trial managers and data coordinators will have access to group allocations and any unblinding will be reported.

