## Data collection and management

### Plans for assessment and collection of outcomes {18a}

Microsoft Access, a database management system (DBMS) of Microsoft Office, will be used to ensure the data safety. SARS-CoV-2 RT-PCR test and HRCT score will be done every fourth day while COVID-19 symptoms evaluation will be done on daily basis to access the time taken for the alleviation of symptoms. Thirty-day mortality will be assessed by the number of deaths per group after 30 days of randomization in all groups. All trial data will be collected by site investigators and two site investigators will enter the data, recheck twice for possible errors separately, and make certain its integrity. Pre-approved questioner regarding demographics of the patient and data collection will be used while all the testing will be done by International Organization for Standardization (ISO) certified laboratory (Shaukat Khanum Laboratory). Principal investigators will visit twice weekly the study site. Trial steering committee members will make unexpected and unplanned visits as well. There is no conflict of financial and non-financial interest with sponsors and researchers.

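### Only the capsule has a placebo, so the blinding claimed for participants and administering staff cannot hold in the syrup (B) and spray (C) arms: two of the three comparisons with placebo

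*Protocol article*

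**What the plan says.** Section {6b} gives the active arms iodine "in 3 different formulations (capsule, syrup, and nasal spray, respectively"), for arms A, B and C. The control is a capsule only: "arm X, will receive a placebo empty capsule, in addition to standard care". The arm list in {11a} repeats this: "Arm X will be receiving a placebo of empty capsule three times a day". It names no dummy syrup or spray for arm X and no dummy capsule for arms B and C.

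Section {17a} nevertheless lists participants, site investigators, care providers, outcome assessors, study coordinators, data managers and statisticians as blinded. Participants are to be blinded by means of the placebo group, and on appearance it says: "Both drugs will look alike, as they will have same packing but unique randomization codes". The abstract and {8} describe the whole trial as placebo-controlled and closed-label.

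On roles, {17a} describes care-provider blinding as achieved "by using site investigators to provide placebo or drugs to participants" and says blinded clinicians assess the clinical outcome. Section {16b} gives implementation of the intervention to co-investigators who do not assess clinical outcomes. Section {18a} says: "All trial data will be collected by site investigators".

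**The concern.** Packing cannot make a liquid or a spray look like a capsule. Since placebo exists only as a capsule, anyone who sees a syrup or spray can tell that it is iodine. The blinding described for the whole trial is therefore not available, for participants and administering staff, in arms B and C.

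The outcome most exposed is time to alleviation of symptoms. It is first among the primary outcomes in Table 1, is evaluated daily ({18a}), and is the endpoint named for sample size re-estimation ({14}). It depends on what the patient reports and on when someone judges recovery complete. Section {11c} adds that "participants will be counselled about the advantages of this study". That counselling goes to every arm and is not differential by itself. It does set an expectation of benefit, and patients who believe they are on active drug can act on that expectation more than capsule patients who may be on placebo.

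If the text stands, a symptom difference in B-X or C-X would be reported as blinded, placebo-controlled superiority although part of it could come from knowledge of treatment.

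**Working it through.** **1. Products by arm ({6b}, {11a})**

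| Arm | Form | Active? | Same form as arm X? |
|---|---|---|---|
| A | capsule | yes | yes |
| B | syrup | yes | no |
| C | nasal spray | yes | no |
| X | empty capsule | no | – |

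The look-alike sentence in {17a} speaks of two drugs; the trial has four products in three forms. It can describe A and X at most.

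**2. Extent.** With 50 per arm ({14}), 4 × 50 = 200, which agrees with the stated total. Arms B and C hold 50 + 50 = 100 of 200 participants, and 100 of the 150 on active drug. Of the comparisons with placebo, A-X has a matching form; B-X and C-X do not.

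**3. Comparisons between routes.** Participants in B and C can both infer that they are on active drug, so B-C is symmetric in this respect. Participants in A cannot be sure, so A-B and A-C are asymmetric.

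**4. Who sees the form.** Section {11c} has health professionals give the product under direct observation, so they see it. Section {26a} says the procedure is explained in detail at consent, so participants probably learn that placebo is a capsule. The document does not state this.

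**5. Who records.** The three role statements do not fit together. In {16b} the implementers are co-investigators without an assessing role. In {17a} site investigators hand out the product and blinded clinicians assess. In {18a} site investigators collect all data. The text leaves open whether one person may do both.

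**6. What a bias could do (assumed range).** The document gives no bias size. Assume no true effect, 50 v 50, two-sided alpha 0.05 (the plan does not state sidedness), and a reporting shift of b SD in favour of iodine. The standard error is √(2/50) = 0.20 SD, and

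P(p ≤ 0.05) = 1 − Φ(1.96 − b/0.20) + Φ(−1.96 − b/0.20).

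| b (SD) | 0 | 0.1 | 0.2 | 0.3 | 0.5 |
|---|---|---|---|---|---|
| Chance of a false positive, one comparison | 5% | 7.9% | 17.0% | 32.3% | 70.5% |

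On the time-to-event scale, assume all 100 patients in a comparison reach the event. The log-rank statistic then has mean √(100/4) × ln(RR) = 5 ln(RR).

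| Spurious rate ratio | 1.0 | 1.1 | 1.2 | 1.3 | 1.5 |
|---|---|---|---|---|---|
| Chance of a false positive | 5% | 7.6% | 14.9% | 25.9% | 52.7% |

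For scale, 50 per arm has 80% power for (1.960 + 0.842) × 0.20 = 0.56 SD, or a rate ratio of about exp(0.56) = 1.75. A bias well below the detectable effect would already inflate the error rate noticeably.

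**The case against.** Much of the masking can survive, and several stronger readings do not.

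- *A reader might infer that all blinding fails in B-X and C-X.* Dosage form unmasks participants and administering staff. It does not by itself unmask the laboratory, the HRCT readers, separate blinded clinicians or the outside analysts named in {17a}. Two of the three primary outcomes are not patient-reported.
- *That participants know they take iodine.* This requires them to know that placebo comes only as a capsule. The consent explanation makes that very likely, but no statement confirms it.
- *That the symptom result is biased.* The document supports a risk. It gives neither the size nor proof that bias occurs.
- *That the person rating symptoms has dispensed the product.* Sections {16b} and {17a} point the other way. What stands is a conflict with {18a}.
- *That data coordinators hold the allocations throughout.* Section {17b} does say "the trial managers and data coordinators will have access to group allocations", but only where unblinding is required. This is an emergency route and does not contradict {17a}.
- *That A-X is securely blinded.* Arm X's capsule is empty and arm A's is filled. Only appearance and packing are said to match; weight and taste are not mentioned.

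It could also be said that a journal article leaves product detail to a full protocol. That does not answer the point: the article states both the arms' products and the blinding method, and the two conflict.

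Timing is a fair objection. Recruitment began on July 30, 2020, and the estimated completion date (February 15, 2022) falls 27 days after publication (January 19, 2022). Changes in conduct may reach few participants; changes in description and interpretation reach all the results.

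**Conclusion.** The point holds. For B-X and C-X, {17a} claims a property that the products in {6b} and {11a} cannot deliver: masking of participants and administering staff. This touches 100 of 200 participants and two of the three comparisons with placebo, and makes A-B and A-C asymmetric. The consequence is a risk of bias, probably favouring iodine, mainly in time to symptom alleviation and much less in RT-PCR and HRCT if those are read without the arm. Its size is unknown; the error rates shown rest on assumed shifts and illustrate sensitivity only.

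The conclusion assumes that no dummy product exists beyond those described and that participants learn the placebo's form. If they did not, the failure would still apply to administering staff. The disagreement among {16b}, {17a} and {18a} on who dispenses and who records is a separate inconsistency that weakens the intended safeguard. The masking claim should be corrected before any B or C symptom result is presented as blinded.

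**What to change.** 1. **Abstract, {8} and {17a}:** state that in B-X and C-X participants and administering staff are not masked to active treatment; that masking there is limited to outcome assessors, laboratory and HRCT readers, and analysts; and that A-X is masked only as far as the filled and empty capsules match.
2. **{16b}, {17a} and {18a}:** reconcile the roles so that whoever dispenses or administers the product does not record symptoms. Use the blinded clinicians already named, and keep arm and dosage form off symptom sheets and off RT-PCR and HRCT requests.
3. **Reporting:** present the B and C symptom results as not participant-blinded and interpret them alongside the masked RT-PCR and HRCT results. RT-PCR should not become a formal gatekeeper: arm C's spray is given close to where the nasopharyngeal swab is taken, and a real symptom benefit need not come with faster clearance.

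The cost is wording, a split of existing staff roles for participants still to be followed, and a more modest claim for B and C. No new product is needed.

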### Intervention description {11a}

In this multi-armed study, ionic-iodine polymer complex will be given using three formulations with 200 mg of elemental iodine to evaluate efficacy for a maximum of 14 days or when the patient is fully recovered.
Arm A will be receiving 200 mg iodine complex capsule three times a dayArm B will be receiving iodine complex suspension syrup form 40 ml three times a dayArm C will be receiving iodine complex nasal spray 2 puffs three times a day.Arm X will be receiving a placebo of empty capsule three times a day.

All patients will receive standard care as per version 3.0 of clinical management guidelines for COVID-19 established by the Ministry of National Health Services of Pakistan COVID-19 guidelines of the study setting.

### Criteria for discontinuing or modifying allocated interventions {11b}

Fixed doses will be given throughout the study and interventional drug administration will be stopped immediately in following conditions.
Patient becomes severely symptomatic during trial conduction.Any adverse drug reaction.Organ failure secondary to any administered drug.Denies/backs off from further participation.

Regardless of any of these conditions, the participant’s data will be retained and analyzed in the trial to follow-up and prevent any loss of data.

### Strategies to improve adherence to interventions {11c}

To improve adherence to the intervention, participants will be counselled about the advantages of this study. All the participants will be monitored regarding compliance to their assigned treatment strategy and health professionals will administer the drugs. As this trial will include quarantined patients, hence direct observational method will be sufficient to make sure compliance and adherence to the interventions.

